## **Background & justification**

The three major Soil-Transmitted Helminths of humans (STH's), *Ascaris lumbricoides* (roundworm), *Necator americanus/Ancylostoma duodenale* (the hookworms) and *Trichuris trichiura* (whipworm) are amongst the most prevalent parasites worldwide. The major means of controlling STH infections is by the periodic administration of one of the four anthelmintics recommended by the WHO: mebendazole (MBD), albendazole (ALB, the most common used anthelmintic to treat STH), levamisole & pyrantel. Currently, for the human STH, large scale mass chemotherapy campaigns are taking place in various parts of Africa, Asia and South America, particularly targeting school children. Although WHO recommends a parasitological check every few years in large scale treatment programmes, these are being conducted infrequently without a coherent long-term strategy and without a standardized monitoring protocol.

During a WHO-World Bank meeting (Washington, Nov 2007) it was decided that monitoring the efficacy of anthelmintics should be a key-issue and a Working Group was established to make recommendations for "Monitoring of drug efficacy in large scale treatment programmes for human STH".

## **Objectives**

### **Overall Objective**

The overall objective is to develop and validate a standard protocol to monitor efficacy of anthelmintics of Soil Transmitted Helminths (STH) in populations with different exposure to anthelmintics.

**Primary objectives**

1. To assess the change in Faecal Egg Counts (FEC) in school age children 14 days following the treatment with a single dose 400 mg of albendazole
2. To monitor efficacy by determining the Cure Rate (CR) and Egg Reduction Rate (ERR)

**Secondary objectives**

1. To evaluate the suitability of the Faecal Egg Count Reduction Test (FECRT) as a standard tool to monitor efficacy i.e. to develop a robust analytical approach that accounts for possible confounding factors
2. To compare the relative performance of the Kato Katz or other qualitative coprological techniques and the McMaster egg counting technique.

**Study sites and population****Study sites**

A total of 7 countries were selected by the working group: Brazil (Minas Gerais State), Cambodia (Kratie), Cameroon (Loum and Yoyo), Ethiopia (Jimma), India (Vellore, Thiruvanamalai), Tanzania (Zanzibar, Pemba Island), Vietnam (Thái Nguyên, Tuyên Quang).

Selection criteria considered by the group in choosing the study sites were:

- The ability of the sites to perform the studies  
e.g. presence of equipped diagnostic facilities, skilled personnel
- A documented history of presence of STH
- A known history of drug selection pressure: high, low or none.

**Study Population**

Schoolchildren between 6 and 18 years old are the focus of this study because of two main reasons:

1. Schoolchildren are the most accessible group. In countries where school enrolment rates are good the group can be easily reach through the school system (Partnership For Child Development, 1999), in area where enrollment is not high non-enrolled siblings could be effectively outreached by promoting advocacy through the schools (Montresor *et al.*, 2001). Therefore it is considered that in each country where

resistance to benzimidazole is suspected, this group will be the easier one to be investigated.

2. Schoolchildren are the one that more probably could harbor resistant species of STH.

Children of primary school age (6 - 18 years) are normally a major target for regular treatment with anthelminthic, because they are the group that usually has the heaviest worm burdens for *A. lumbricoides* and *T. trichiura*, and are steadily acquiring hookworm infections. In addition, they are in a period of intense physical and intellectual growth (Bundy *et al.* 1992; Crompton and Nesheim, 2002). Deworming school-age children has a considerable benefit on their nutritional status (Stoltzfus *et al.*, 1996, Curtale *et al.*, 1995), physical fitness, appetite, growth (Stephenson *et al.*, 1993) and intellectual development (Nokes *et al.* 1994).

### **Ethical issues**

The overall protocol of the study has been reviewed by the Ethics committee of the Faculty of Medicine, Ghent University, Belgium on 15/07/2008. A positive advice was given on 30/06/2008 (Nr B67020084254) (Annex 1). A sample of consent form and the accepted protocol is also attached.

For each proposed study a separate ethical clearance will be obtained.

### **Parasitological technique to determine FEC**

The standard coprological technique to be used will be the McMaster method, a user-friendly method widely practiced in Veterinary Medicine. The McMaster method is a quantitative method for analysis of FEC. For each sample one chamber (two compartments) will be counted (sensitivity of 50 eggs/gram) (Annex 2.1). A video showing the McMaster technique will be made and provided to all participating laboratories.

McMaster slides will be provided free by the coordinating group

### **Preliminary Comparative study of the coprological techniques**

As there has been relatively little use of the McMaster method for human coprologic examination, a pilot study comparing the Kato Katz (Annex 2.2) and McMaster method (Annex 2.1) should be undertaken on 200 samples at each study site. From the 200 samples at least 100 samples should be positive for STH in either technique at each study site.

As the Kato Katz method has an estimated sensitivity threshold of 24 eggs/gram of faeces, two McMaster chambers (4 compartments, sensitivity of 25) will be counted for the comparative study.

In the case that the local routine coprological technique is not the Kato Katz , the McMaster method should be compared with the routine technique in use.

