### Procedure

1. Weigh 2 grams of faeces in a plastic beaker (100 ml).
2. Add 30 ml of the flotation fluid saturated salt solution,
3. Homogenise and pour the faecal suspension 3 times through a tea strainer to withhold the large debris.
4. Homogenise the filtrate by pouring it at least 5 times from one beaker to another and fill up one side of a regular McMaster counting chamber by using a pasteur pipette. Repeat for the other side.
5. Allow the counting chamber to stand for 2 minutes, place under a light microscope and examine using a 100x magnification. All the eggs under the two separate grids are counted (this represents a volume of  $2 \times 0.15$  ml)
6. The number of eggs per gram of faeces is obtained by multiplying the total number of eggs under the two grids by 50. The sensitivity of the test is 50.

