## **Annex 2.2 - Kato-Katz technique-cellophane faecal thick smear**

### **Materials and reagents**

1. Applicator sticks, wooden.
2. Screen, stainless steel, nylon or plastic 60-105 mesh.
3. Template, stainless steel, plastic, or cardboard . Templates of different sizes have been produced in different countries. A hole of 9 mm on a 1 mm thick template will deliver 50 mg of faeces; a hole of 6 mm on a 1.5 mm thick template, 41.7 mg; and a hole of 6.5 mm on a 0.5 mm thick template, 20 mg. The templates should be standardized in the country and the same size of templates should always be used to ensure repeatability and comparability of prevalence and intensity data.
4. Spatula, plastic.
5. Microscope slides (75 x 25 mm).
6. Hydrophilic cellophane, 40-50 mm thick, strips 25 x 30 or 25 x 35 mm in size.
7. Flat-bottom jar with lid.
8. Forceps
9. Toilet paper or absorbent tissue.
10. Newspaper.
11. Glycerol-malachite green or glycerol-methylene blue solution (1 ml of 3% aqueous malachite green or 3% methylene blue is added to 100 ml of glycerol and 100 ml of distilled water and mixed well). This solution is poured onto the cellophane strips in a jar and left for at least 24 h prior to use.

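### The pilot compares Kato-Katz with a two-chamber McMaster count, but the trial reads one chamber, so the pilot's low-count sensitivity does not apply directly to the trial's method

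*Protocol*

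**What the plan says.** The trial's standard method is set in the protocol section *Parasitological technique to determine FEC*: "For each sample one chamber (two compartments) will be counted (sensitivity of 50 eggs/gram". Annex 2.1 agrees and multiplies the eggs under the two grids by 50.

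The section *Preliminary Comparative study of the coprological techniques* gives the reason for a pilot, "As there has been relatively little use of the McMaster method for human coprologic examination", and its size: it "should be undertaken on 200 samples at each study site". It then departs from the standard reading. The premise is "As the Kato Katz method has an estimated sensitivity threshold of 24 eggs/gram of faeces", and from this it follows that "two McMaster chambers (4 compartments, sensitivity of 25) will be counted for the comparative study". The pilot serves the second secondary objective, "To compare the relative performance of the Kato Katz or other qualitative coprological techniques and the McMaster egg counting technique".

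On the Kato-Katz side, Annex 2.2 lists templates of 50, 41.7 and 20 mg with factors of 20, 24 and 50. On the choice of size it says: "The templates should be standardized in the country and the same size of templates should always be used". No section names one size for all sites. Where Kato-Katz is not the local routine, the pilot may use the routine technique as comparator instead.

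**The concern.** The pilot is justified by limited experience with McMaster in human samples, and it is the only planned comparison of McMaster with another technique. Yet the reading it evaluates uses twice the volume that the efficacy study will read. A sensitivity estimate from the pilot would therefore be too favourable to the trial's method where few eggs are present.

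Cure rate, one of the two efficacy measures, depends on whether any egg is seen after treatment. The minimum of 150 epg applies at the first sampling only and to any one species; the other species are also counted at the second sampling, with no minimum of their own. Low counts therefore enter the cure rate.

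A second gap lies in the comparator. The two-chamber reading was chosen to match 24 epg, but the protocol does not secure that Kato-Katz will be read at 24 epg at every site.

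**Working it through.** **Inputs.** McMaster: 2 g of faeces, 30 ml of flotation fluid, 0.30 ml read per chamber (Annex 2.1). Kato-Katz: templates of 50, 41.7 and 20 mg (Annex 2.2).

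**Step 1: reproduce the stated thresholds.** Epg per egg = fluid volume / faeces weight / volume read.

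- One chamber: 30 / 2 / 0.30 = 50 epg.
- Two chambers: 30 / 2 / 0.60 = 25 epg.
- Kato-Katz: 1000 / 50 = 20; 1000 / 41.7 = 23.98, or 24; 1000 / 20 = 50.

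All the stated figures reproduce. In stool mass, one chamber reads 0.30 × 2/30 = 0.020 g (20 mg) and two chambers read 40 mg. Two chambers thus match the 41.7 mg template, and one chamber matches the 20 mg template.

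**Step 2: detection by true egg density.** Assume a Poisson count (eggs randomly mixed, full recovery in both techniques). Then P(at least one egg) = 1 − exp(−epg / factor). For example, at 50 epg one chamber gives 1 − exp(−1) = 63% and two chambers give 1 − exp(−2) = 86%.

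| True epg | McMaster, 1 chamber | McMaster, 2 chambers | Gap (points) | Kato-Katz 50 mg | Kato-Katz 41.7 mg | Kato-Katz 20 mg |
|---|---|---|---|---|---|---|
| 25 | 39% | 63% | 24 | 71% | 65% | 39% |
| 50 | 63% | 86% | 23 | 92% | 88% | 63% |
| 100 | 86% | 98% | 12 | 99% | 98% | 86% |
| 150 | 95% | 99.8% | 5 | 99.9% | 99.8% | 95% |

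**Step 3: relate this to counts after treatment.** The footnote to the sample size works with a null efficacy of about 80%. As an illustration only, a child at the 150 epg minimum with an 80% reduction is left with 150 × 0.20 = 30 epg. One chamber then detects 1 − exp(−0.6) = 45%, and two chambers 1 − exp(−1.2) = 70%.

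**Step 4: mean egg count.** The count is multiplied by its own factor, so its expectation is the true epg with one or two chambers. Only the counting noise changes. At 100 epg the coefficient of variation is √(50/100) = 0.71 with one chamber and √(25/100) = 0.50 with two.

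**Step 5: template.** With the 41.7 mg template the pilot compares 25 with 24 epg, as intended. With the 20 mg template it compares 25 with 50 epg, and the matching is lost. At 25 epg, Kato-Katz detection runs from 39% to 71% across the three listed templates.

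**The case against.** The two-chamber reading is a stated and defensible choice. Comparing techniques on nearly equal stool mass (40 against 41.7 mg) separates the technique from the volume read, and the secondary objective asks about relative performance, not about validating one chamber. The protocol does not credit the trial with 25 epg; it confines that figure to the pilot. The one-chamber reading is contained in the two-chamber count, and per-chamber recording could be left to the case report form or the SAP. No section says that any site will use a 50 or 20 mg template, and each site's comparison is made within that site.

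Most of this stands. It justifies counting two chambers, but it does not supply the one-chamber result that the trial's method needs. The template question is an unresolved gap between two sections, not a planned difference.

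Three stronger readings are tempting, and the documents do not support them.

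- *A reader might infer that nothing from the pilot transfers.* Agreement in mean egg count does carry over, with more noise, and the detection gap is small at and above 150 epg.
- *A reader might infer a fixed 6% McMaster bias* from the instruction "Add 30 ml of the flotation fluid saturated salt solution" to 2 g, since 32 / 2 / 0.30 = 53.3 rather than 50. This assumes that 2 g of faeces adds a full 2 ml. The protocol's own convention gives 50 exactly, and a constant factor cancels in percentage reductions and leaves egg-positive status unchanged.
- *A reader might infer that the Kato-Katz factors are wrong,* because the template dimensions imply different densities (0.79, 0.98 and 1.21 mg/mm³). Nothing in the documents shows which nominal mass is right, so no replacement factor can be derived.

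**Conclusion.** The point holds in a limited form. The pilot's sensitivity at low counts describes a reading that the efficacy study does not use. Under the Poisson assumption it overstates one-chamber detection by about 23 to 24 points at 25 to 50 epg, 12 points at 100 epg and 5 points at 150 epg. Clumped eggs or incomplete flotation would change the size of the gap but not its direction. The result carries over least to positivity and cure rate after treatment, to the extent that residual counts are low; the protocol does not state what residual counts it expects. The expected mean egg count, and so an egg reduction rate based on sample means, is not affected.

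Separately, the 24 epg used to justify two chambers presumes a template that no section requires. This needs reconciling, but it is not evidence that templates will differ. The change is worth making because it costs little and lets the pilot inform the method that the trial actually uses.

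**What to change.** In *Preliminary Comparative study of the coprological techniques*, keep the two-chamber count but require each chamber to be recorded separately. Report McMaster against Kato-Katz for one chamber (the trial's method, 50 epg) and for two chambers (25 epg), from the same 200 samples per site. The one-chamber report is equally useful at sites that use another routine technique as comparator.

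Reconcile that section with Annex 2.2. Either specify the 41.7 mg template (factor 24) for the pilot at Kato-Katz sites or, where another size is used, record it and state that site's threshold. The reason for 41.7 mg is only that the section's own 24 epg presumes it.

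The cost is one more count column and one more analysis, and a non-routine template for the pilot samples at some sites. No additional stool samples are needed.

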## **Efficacy study**

### Experimental design

Following obtaining informed consent, schoolchildren in the target age range group will be recruited and asked to provide a recent stool sample (an interval of less than 4 hours) that will be processed to determine the FEC for each STH present. A small subsample of faecal samples will be also collected for coproculture to identify the hookworms species present and preserve parasite material for subsequent analysis (Annex 2.3).

All children providing stool samples will be treated with Albendazole (GSK®) single tablet of 400mg under supervision (chewing + water). The Albendazole will be provided (free) by the coordinating group.

14 to 30 days after treatment a second faecal sample will be collected from the children to determine again FEC. Only children infected with a minimum of 150 eggs/gram of any species of STH (i.e. *Ascaris* or hookworms or *Trichuris*) at the first sampling should be included in the second sampling. However, for the other STH present FEC should also be determined at the second sampling.

### Sample size

The initial number of schoolchildren to sample will depend on the prevalence of the STH in the study region as a minimum of 250 infected children with a minimum of 150 eggs/gram of any species of STH (i.e. *Ascaris* or hookworms or *Trichuris*) should be recruited at each study site e.g. with an expected prevalence of 50% for any specific STH 500 schoolchildren should be enrolled in the first sampling.

If the epidemiological scenario allows, individual study sites may include two groups of children (each with 250 infected children with a minimum of 150 eggs/gram of any species of STH): (1) a group of children resident in areas where the government had, for  $\geq$  than 3 years, a regular (one or two treatments/year) mass drug administration program with a benzimidazole anthelmintic (albendazole or mebendazole) and (2) a group of children resident in areas where there is no mass drug administration program.

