### Data analysis

Both CR and ERR will be considered to monitor to efficacy.

To avoid distortion due to the density dependant effect, the CR and ERR will be also calculated separately in the different classes of intensity at baseline.

---

 Statistical power analyses, based on random simulations of correlated overdispersed FEC data reflecting the variance-covariance structure in a selection of real FEC data sets, suggest that a sample size of up to 200 individuals ( $\alpha = 0.05$ , power = 80%) is required to detect a 10 percentage point drop from a null efficacy of  $\sim 80\%$  (mean percentage FEC  $\Delta$  per individual) over a wide range of infection scenarios. Standard power analyses for proportions also indicate that the detection of a  $\sim 10$  percentage point drop from a null cure rate requires sample sizes ranging up to 200 (the largest samples being required to detect departures from null efficacies around 50%). Given an anticipated non-compliance rate of 25%, a sample of 250 individuals with  $>250$  egg/g pre-treatment should therefore be followed up for post-treatment FEC data at each study locality.

The following indexes should be used to monitor drug efficacy:

Cure rate

$$[N \text{ egg positive post-treatment} / N \text{ egg positive pre-treatment}] * 100$$

Mean FEC  $\Delta$  per individual

$$\frac{\sum_{i=1}^{i=N} [T1_i - T2_i]}{N}$$

Where T1 = pre-treatment FEC, T2 = post-treatment FEC, and  $i$  = the  $i$ th subject.

Mean percentage FEC  $\Delta$  per individual

$$\frac{\sum_{i=1}^{i=N} \{ [T1_i - T2_i] / T1_i \} * 100}{N}$$

Percentage  $\Delta$  in the sample mean FEC

$$\{ [\text{sample mean T1} - \text{sample mean T2}] / \text{sample mean T1} \} * 100$$

Confidence intervals for these indexes can be generated by a standard method for proportions in the case of cure rate (the exact binomial method) and by bootstrap resampling methodologies for the FEC  $\Delta$  indexes.

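### The target of 250 children per site counts infection with any STH species, so it does not secure the stated 80% power for each species

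*Protocol*

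**What the plan says.** **Recruitment.** Protocol, Sample size, sets a minimum of 250 infected children per site "with a minimum of 150 eggs/gram of any species of STH" and lists Ascaris, hookworms and Trichuris as alternatives. A child counts once, whichever species qualifies it. The worked example in the same paragraph then takes a 50% prevalence of one particular species and arrives at 500 children to screen, which gives 250 carriers of that one species.

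**Measurement.** Protocol, Experimental design, has the baseline stool "processed to determine the FEC for each STH present". Only children who reach the threshold for some species are sampled again, but "for the other STH present FEC should also be determined at the second sampling".

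**Power.** The footnote under Data analysis states, for alpha 0.05 and 80% power, that "a sample size of up to 200 individuals" "is required to detect a 10 percentage point drop from a null efficacy of" about 80% (mean percentage change in egg count per child). For cure rates it says that detecting a drop of about 10 "percentage point drop from a null cure rate requires sample sizes ranging up to 200", with "the largest samples being required to detect departures from null efficacies around 50" percent. It then allows for 25% non-compliance and arrives at 250 per locality. No minimum per species appears in any of these sections.

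**The concern.** The recruitment rule and the power statement use different units. The footnote's 200 is the number behind one proportion or one mean percentage reduction. The recruitment rule fills 250 places with carriers of any of three species. If efficacy is read per species, as the per-species counts imply, the denominator for a species is the number of its carriers, which may be well below 250.

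At stake is how a negative result is read. At a site where one species is carried by a minority of the children, finding no drop in efficacy could reflect too few carriers rather than preserved efficacy. A reader who takes the footnote at face value would credit that result with 80% power. This matters for a study whose overall objective is a standard monitoring protocol for populations with different drug exposure.

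**Working it through.** **Inputs.** From the Protocol: alpha 0.05, power 80%, a 10-point drop, up to 200 evaluable, 25% non-compliance, 250 per site. Not in the Protocol: the share f of the 250 who carry a given species, taken here as 1, 0.5 and 0.33. Sidedness is not stated; two-sided is used because it reproduces the Protocol's figure and one-sided (153) does not.

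**Step 1: reproduce the stated 200.** One-sample test of a proportion against a fixed null, normal approximation:

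n = [z₁·√(p0(1−p0)) + z₂·√(p1(1−p1))]² / (p0−p1)², with z₁ = 1.960 and z₂ = 0.842.

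For 50% against 40%: (1.960×0.5 + 0.842×0.490)² / 0.01 = (0.980 + 0.412)² / 0.01 ≈ 194. The largest value found for a 10-point drop is 195 (55% against 45%). This agrees with the Protocol's upper limit of 200 and with its remark that the maximum lies near 50%.

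**Step 2: the number needed at other nulls.** The same formula gives 137 at a null cure rate of 80%, 86 at 90% and 53 at 95%. The 200 is therefore a worst case.

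**Step 3: carriers available.** Two readings are carried through, because the footnote can be taken to mean 250 actually followed up or 250 before losses.

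- All followed up: 250f, so 125 at f = 0.5 and 82.5 at f = 0.33.
- After 25% loss: 250×0.75×f = 187.5f, so 93.75 at f = 0.5 and 61.9 at f = 0.33.

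**Step 4: power for a 10-point drop.** Power = Φ{[0.10·√n − z₁·√(p0(1−p0))] / √(p1(1−p1))}. Example, n = 125, 50% against 40%: (1.118 − 0.980)/0.490 = 0.282, so power is 61%.

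| Share carrying the species | Null 50% | Null 80% | Null 90% |
|---|---|---|---|
| All (250 / 187.5) | 89% / 79% | 96% / 90% | 99% / 97% |
| Half (125 / 93.75) | 61% / 49% | 77% / 66% | 91% / 83% |
| A third (82.5 / 61.9) | 44% / 35% | 61% / 50% | 79% / 69% |

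In each cell the first figure assumes all are followed up and the second 25% loss. Exact binomial power after loss is generally lower and moves in steps with n: at n = 62 and null 50% it is 28% against 35%.

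**Step 5: share needed for 80% power.** Required n divided by 250, or by 187.5:

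| Null cure rate | All followed up | After 25% loss |
|---|---|---|
| 50% | 194/250 = 78% | 194/187.5, above 100% |
| 80% | 137/250 = 55% | 73% |
| 90% | 86/250 = 34% | 46% |
| 95% | 53/250 = 21% | 28% |

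**Step 6: egg reduction.** The simulation cannot be rerun because its variance inputs are not given. Scaling from the statement that 200 gives 80%, power = Φ[(1.960+0.842)·√(n/200) − 1.960]. This gives 60% / 48% at f = 0.5 and 44% / 34% at f = 0.33.

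**Step 7: detectable drop.** Solving Step 1 for the drop at 80% power from a null of 50% gives 14.3 points at n = 94, 17.5 points at n = 62 and 10.2 points at n = 187.

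**The case against.** The strongest reply is that 200 is an upper bound. Where the expected cure rate is high, far fewer children suffice: at a null of 90%, a species in half the children has over 80% power on either reading of follow-up. Even at a null of 50%, a species in about 78% of 250 followed-up children reaches 80%. This stands. A reader might infer that the power claim fails for every species not carried by all enrolled children; the footnote's own wording and Step 2 rule that out.

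A second reply is that the worked example uses the prevalence of one species, so the 250 may be meant per species. The example does make the unit unclear, but it does not override the rule itself, which lists the three species as alternatives. Co-infection also helps, since the carriers of the three species may add up to more than 250, but nothing guarantees how many carry any one of them.

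A third reply is that part of the shortfall in the after-loss figures comes from the allowance for non-compliance rather than from the species count. That is fair: 250 less 25% leaves 187.5, and worst-case power is then about 79% even if every child carries the species. The species effect is visible without it, in the figures for 250 followed up.

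Two further inferences are tempting and unsupported. No section proposes pooling egg counts over species; the Protocol counts each one separately. And whether a species' analysis set should exclude children below 150 eggs/gram for that species is commonly settled in the SAP, which is not at hand, so the Protocol's silence on it is no error.

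**Conclusion.** The point holds in a limited form. The recruitment target and the power statement use different units, and the target does not secure 80% power for a 10-point drop for each species. The gap is large for a species in a third to a half of the children at the null near 50% for which the footnote's largest cure-rate sample is required: 44% to 61% power with full follow-up, 35% to 49% after 25% loss. It narrows as the null rises and closes at a null of 90% for a species in half the children.

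These figures rest on assumed species shares, a one-sample two-sided test that matches the Protocol's 200, and the normal approximation; the egg-reduction figures also rest on scaling. They do not show that any particular site or species is under-powered, because the Protocol gives no expected shares. The weakness is that the 80% claim is stated without the per-species condition on which it depends.

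**What to change.** No extra children are needed.

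1. In the footnote, state that the 80% power claim applies per species, and only where the expected evaluable number for that species reaches the required n: for cure rate about 194 at a null of 50%, 137 at 80%, 86 at 90% and 53 at 95%.
2. For each site, give the expected evaluable number for each species and the drop detectable with it, for example from a null of 50%: 14.3 points at 94 children and 17.5 points at 62.
3. Reword the target and the worked example under Sample size so that both use the same unit, either any species or one named species.

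The work is limited to restated power figures and a few sentences. The downside is that the stated figures become less favourable for the rarer species.
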